## I.3 Number of Subjects

- 1. Specify the number of subjects to be enrolled in total across all sites:       or  N/A this is not a multicenter study.
  2. Specify the number of subjects to be enrolled at the Tufts site. Subjects who sign an ICF are considered “enrolled”. For studies that have a separate screening ICF, this number is the number of subjects who sign a screening ICF: 200

1. Provide the rationale for enrolling this number of subjects at the Tufts site: See sample size section above.
2. Estimate the number of subjects expected to be enrolled at the Tufts site (i.e. sign the screening or study ICF) as well as the number needed to complete the study at the Tufts site: See sample size justification above.
3. If a large number of withdrawals and/or dropouts is expected, explain why: See sample size justification above.

##

## I.4 Data Management

- 1. Describe the data analysis plan, including descriptions of the data: See above section on statistical analysis
  2. Describe the steps that will be taken to secure the data (e.g., training, authorization of access, password protection, encryption, physical controls, certificates of confidentiality, and separation of identifiers and data) during storage, use, and transmission:

Personal health information will be collected and used by the Principal Investigator and his authorized co-investigators as part of this research protocol. All information collected throughout the study will be kept strictly confidential and only entered into the RedCap secure data server. For purposes of analysis all data extracted from the RedCap server will be de-identified. The de-identified data will be entered into a password protected spreadsheet stored on a secure hospital server. Subjects will only be identified by a unique ID. No identifiable information will be stored on any mobile devices. There will be no patient interventions performed for this study. All data will be kept and stored securely as per regulation

- 1. Describe any procedures that will be used for quality control of collected data: NA

## I.5 Randomization

Will subjects be randomized?

**Yes  No**

# Drugs or Devices

- 1. Will the research involve drugs?

**Yes  No**

- 1. Will the research involve devices?

**Yes  No**

If **Yes**, respond to all of the following:

1. If the device has an IDE or a claim of abbreviated IDE (non-significant risk device) identify the holder of the IDE/Abbreviated IDE:      The device used in this study is an FDA approved device. Please see submitted documentation in IRB application.
2. Describe your plans to store, handle, and administer study devices so that they will be used only on subjects and be used only by authorized investigators (if the control of the devices used in this protocol will be accomplished by following an established, approved organizational SOP, please reference that SOP in this section):      The device used in this study is approved for clinical use by the FDA. There is no reason that it can not be used for non-research purposes by the investigators. As described in detail above, if the device is to be used for research purposes all of the aforementioned protocols and informed consent process will be followed prior to using the device for research purposes.
3. Specify who will be responsible for the costs of implantation or placement of the device in subjects’ bodies?:       or N/A, the device will not be implanted or placed in the body.
4. Specify who will be responsible for the costs of removing the device from subjects’ bodies?       or N/A, the device will not be removed from the body.
5. Specify the cost of the device and who will be responsible for the cost:       or N/A, the device will be provided free of charge.
6. Who on the research team, in addition to the Principal Investigator, will be accountable for device(s):      The co-investigators
7. Who will interface with the sponsor:      There is no study sponsor
8. The study device or procedure (including beneficial health care procedures) will be available to subjects after participation in the study: Yes N/A
9. Handouts or instructions sheets that will be given to subjects on how to use study device(s) have been submitted to the IRB: Yes N/A

# Study Administration

## K.1 Setting

1. Describe the sites / locations where your research team will conduct the research: Tufts Medical Center
2. The research will take place at an international site, and the [International Research Guidance](https://eirb.tuftsmedicalcenter.org/IRB/sd/Doc/0/48BQMF8656K4P76QU0ERKMDL6A/International%20Research%20Guidance_Downloaded%20from%20IRB%20website_09.06.19.docx) and [International Checklist](https://eirb.tuftsmedicalcenter.org/IRB/sd/Doc/0/4FUMCVJNRQF4T54J3AVET8NU33/International%20Research%20Checklist_071519.docx) were utilized:  Yes  N/A

## K.2 Registration

1. *Describe the steps the research team will take to ensure that a subject is appropriately enrolled or registered in the study prior to receiving any study intervention (e.g. describe and submit any protocol eligibility checklist that will be used, specify who on the research team will confirm eligibility and that consent was documented, etc.):* As noted above the investigator and co-investigators will determine subject eligibility through review of the echocardiography and right heart catheterization schedules. Once patients are identified the patients will be approached regarding their interest in participation in the study. The step by step procedures to be followed have been outlined in the informed consent form.

## K.3 Resources Available

1. Describe the roles/tasks of each research team member here (or alternatively, you may submit any current Delegation of Authority Log you may have which already has this information completed):

All research team members will participate in subject screening, enrollment, consent, data collection, and performing bedside ultrasound examinations.

1. Describe the qualifications (e.g., training, experience) of the PI and research team to perform their roles. Provide enough information for the IRB to determine the PI and research team are qualified to conduct the proposed research. Alternatively, you can submit the current CVs for the research team instead:

[name] is a board certified cardiologist and an Associate professor of medicine at Tufts University with an extensive background in clinical and non-clinical research. Drs. [name] and [name] are board certified in cardiology and pulmonology/critical care, respectively, and are currently completing advanced clinical fellowship training at Tufts, They have both been involved in the design and implementation of multiple retrospective and prospective clinical studies.

1. Describe the coverage plan to address any issues (including subject safety issues) that occur while the PI is away and/or unavailable. The research team member designated to serve as the acting PI in the PI’s absence should have similar training and expertise as the PI: [name] will serve as the acting PI should any issues arise when [name] is unavailable.
2. Describe the process to ensure the research team members have adequate oversight and are adequately trained regarding the protocol, study procedures, and their roles and responsibilities: The research team includes the investigator and two co-investigators. All three members of this team participated in developing the research question and protocol. They are all fully aware of the research protocol, study procedure, and their roles. If any amendments to the protocol are made all three members of the research team will be informed prior to said amendments. All research team members have confirmed their participation in the study and have agreed to remain up-to-date with any changes in the study protocols and/or procedures.
3. Medical or psychological resources that subjects might need, such as for emergencies or medical issues, are available for the study: Yes  N/A

##

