# Enrollment and Withdrawal

## D.1 Inclusion Criteria

- 1. Describe the criteria that define who will be **included** in the study as a numbered list:
- All patients who are cared for at Tufts Medical Center and:
  - Provide informed consent
  - Age greater than or equal to 18 years old
  - Undergo bedside FoCUS examination with the KOSMOS portable ultrasound device
  - Have had a TTE within 30 days, or have had a TTE ordered by the primary treating team and/or have had/are scheduled for a right heart catheterization with calculation of stroke volume and cardiac output

##

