# Study Design

## F.1 Study Timelines

- 1. Describe the duration of an individual subject’s participation in the study:

Participants will be required to allow a Focused cardiac ultrasound be performed at the time of enrollment. Following this study there is no further requirement from the subject. The research team will follow up on the results of the subjects formal echocardiogram and/or right heart catheterization by reviewing the patient’s medical records if it is not available at the time of enrollment. After this information has been collected the subject’s participation will cease.

- 1. Describe the duration anticipated to enroll all study subjects at the Tufts study site:

12 months

- 1. Describe the estimated date for investigators to complete this study (complete primary analyses):

December 2021.

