- Participants will then undergo the KOSMOS ultrasound evaluation at the time of enrollment or the earliest convenient time after enrolling in the study.
- The TTE and/or right heart catheterization data will be collected and compared with the results of the KOSMOS ultrasound.

*Please also describe the following concerning procedures:*

- - - - 1. How individuals will be screened for eligibility. Specify screening that will take place prior to informed consent and screening that will take place after informed consent:

Screening will begin through identifying individuals who are scheduled to undergo transthoracic echocardiogram and/or right heart catheterization at Tufts medical center. Patients who have recently underwent an echocardiogram may also be included if they are identified by the study team as potentially eligible for participation. There will be no additional screening prior to consent. Following consent the patient’s medical history will be evaluated by questioning the patient and, when necessary, reviewing the patient’s medical records for exclusion criteria. If no exclusion criteria are identified at this point then the patient will begin the protocol as described above.

- - - - 1. Procedures being performed to monitor subjects for safety or to minimize risks:

All data collected will be documented in the case report form in RedCap, which is stored on the Tufts secure server.

- - - - 1. All drugs and devices used in the research, their regulatory approval status, and the purpose of their use:

The KOSMOS device used in this project is an FDA approved ultrasound device that is available for commercial sale. It will be used to perform the bedside cardiac ultrasound as discussed above.

- - - - 1. The source records that will be used to collect data about subjects. (Attach all surveys, scripts, and data collection forms.):

See attached RedCap CRF

1. Is there a placebo control arm?

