## I.2 Sample Size Justification Statistical Analyses

1. Describe the statistical analyses that will be performed for this study:

All patients who are enrolled will be included in the analysis and the data will be analyzed according to the intention-to-treat principle, with the exception of patients who are found to have moderate or greater regurgitant valvular disease following enrollment. Continuous variables will be summarized as either mean and standard deviation or median and interquartile range, as appropriate. Categorical variables will be summarized by frequency and percentage. The Chi-square or the Fisher’s exact test will be used to compare discrete variables, and the Student’s *t* test or Mann-Whitney U-test will be used to compare continuous variables, as appropriate.

First, the differences between the FoCUS and TTE LEVFs, and the differences between the FoCUS and right heart catheterization stroke volumes and cardiac outputs, will be evaluated for normality bot visually and statistically. This will be done by visual evaluation of quantile-quantile plots, and by applying the Shapiro-Wilk test.^11^ Second, we will evaluate for the presence of proportional bias by performing a regression analysis.^12^ Third, in the case of paired measurements (i.e. if a patient has more than one FoCUS examination performed), we will perform a test for autocorrelation. If the autocorrelation is determined to be non-negligible a correction for the use of paired measurements will be applied.^12^ Finally, the agreement between the FoCUS and TTE LVEF’s will be evaluated through the construction of a Bland-Altman plot along with the mean difference (bias), 95% limits of agreement (LOA), and mean error – along with their corresponding 95% confidence intervals.^13^

1. Provide a sample size justification:

Based on a 95% agreement between FoCUS and formal echocardiography, and a 5% error margin, we anticipate that we would need 73 patients with adequate windows to obtain an AI LVEF. As not all patients may have adequate windows to calculate a biplane method of disks summation (modified Simpson’s rule) and individuals may be found to have moderate or great regurgitant valvular disease following formal TTE, we will aim to recruit 130 patients for the LVEF component of this project.

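### Where the reference test precedes the KOSMOS scan, nothing masks the operator to its result or locks the automated reading first

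*Protocol*

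**What the plan says.** Section K.3 describes the team ("The research team includes the investigator and two co-investigators") and its tasks: "All research team members will participate in subject screening, enrollment, consent, data collection, and performing bedside ultrasound examinations".

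The reference test may come before or after the scan. For TTE, section D.1 accepts patients who "Have had a TTE within 30 days, or have had a TTE ordered by the primary treating team". For catheterization it accepts those who "have had/are scheduled for a right heart catheterization with calculation of stroke volume and cardiac output", without a time limit. Section F.1 has the team look up the reference result later only "if it is not available at the time of enrollment", so it expects some results to be on file already.

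Section F.2 gives the sequence: consent, then baseline data from the patient and/or the chart, then the KOSMOS scan, then comparison with the reference. It describes screening as starting from scheduled tests and adds: "Patients who have recently underwent an echocardiogram may also be included if they are identified by the study team as potentially eligible".

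Section I.2 foresees repeated scans ("if a patient has more than one FoCUS examination performed"). It plans an autocorrelation test and, if needed, a correction for repeated measurements. It also counts only patients with adequate windows toward the required numbers, but gives no criterion for adequacy.

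No section masks the operator, separates the person who scans from the person who abstracts the reference, or orders the recording of the two values. Section G.2 limits pre-consent review to what eligibility needs, which is a privacy limit and not masking. Section I.4 answers NA on quality control of collected data.

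**The concern.** The study measures agreement between an automated reading and a reference, and section C hypothesises that the two will match well. Computing the LVEF, stroke volume and cardiac output is automatic; obtaining the input is not. The operator chooses the probe position and the loop, decides whether the windows suffice, and can retake a view that was never written down. An operator who has seen an LVEF in the chart can, without intending to, stop at the reading that looks right or declare the windows inadequate when the reading looks wrong.

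Both behaviours shrink the spread of the differences, and with it the limits of agreement. The error runs toward the hypothesis, and a larger sample does not remove it. Section B.1 itself faults visual LVEF assessment for its exposure to subjective bias, so protecting the index reading matters to the study's own rationale.

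**Working it through.** **1. Can the operator know the reference value?**

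| Step | Source | What follows |
|---|---|---|
| Reference may predate the scan | D.1, F.1 | The value may be in the chart on the day of the scan |
| Chart is used before the scan | F.2 | Someone on the team has the record open first |
| All three investigators take part in screening, data collection and scanning | K.3 | That person may also be the one who scans |
| Masking, or recording the automated value first | no section | Nothing prevents it |

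For reference-first patients the answer is yes. If the reference test follows the scan, its value does not yet exist. The protocol does not give the share of each group.

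**2. How much room is there for operator judgement?** The planned sizes follow from n = z²p(1−p)/d², with 95% confidence assumed (z = 1.96):

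- LVEF: 1.96² × 0.95 × 0.05 / 0.05² = 72.99, so 73, as stated.
- Stroke volume and cardiac output: 1.96² × 0.90 × 0.10 / 0.10² = 34.57, so 35, as stated.

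Recruitment targets are 130 and 70. The plan thus tolerates losing (130 − 73)/130 = 44% for LVEF, partly to regurgitation found later, and (70 − 35)/70 = 50% for stroke volume and cardiac output. Inadequate windows are a stated reason in both, so a large allowance rests on an operator judgement without a criterion.

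**3. What could selection do to the limits?** The documents give no figure for the frequency of retakes or the correlation of their errors, so everything here is assumed. Let two readings have normal errors with mean 0, SD 1 and correlation ρ against the reference, and let the operator keep the closer one. Then

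E[min(e₁², e₂²)] = 1 − (2/π)√(1 − ρ²).

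If this happens in a fraction q of patients, the SD of the differences, and so the width of the limits, is multiplied by √[1 − q(2/π)√(1 − ρ²)].

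| ρ | q = 25% | q = 100% |
|---|---|---|
| 0 | √(0.75 + 0.25 × 0.363) = 0.917 (8% narrower) | √0.363 = 0.603 (40%) |
| 0.5 | √(0.75 + 0.25 × 0.449) = 0.929 (7%) | √0.449 = 0.670 (33%) |
| 0.8 | √(0.75 + 0.25 × 0.618) = 0.951 (5%) | √0.618 = 0.786 (21%) |

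Two readings compared with the same reference share its error, any true change since it was taken and any patient-specific error of the algorithm. A high ρ is therefore more plausible than 0.

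**4. The same in LVEF points, by simulation.** Assume an SD of the difference of 8 points, a within-patient repeat SD of 3 to 6 points, and the closest of two or three readings kept. The half-width of the limits is 1.96 × 8 = 15.7 points without selection. It falls to 14.1–15.0 if selection occurs in 25% of patients and to 12.4–14.3 if it occurs in 50%.

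**The case against.** The strongest case for the plan has five parts.

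- **Scheduled patients look like the main route.** Sections F.2, G.2 and K.2 identify patients from the lists of scheduled tests; recently tested patients are an addition. A reader might infer that the whole cohort is exposed. It is not. This stands and confines the point to reference-first patients.
- **Eligibility does not require reading the TTE report.** A reader might infer that checking valve disease forces the investigator to see the LVEF. Section D.2 excludes only known regurgitation, section F.2 has the patient questioned and records reviewed when necessary, and section I.2 removes regurgitation found later. This stands: the protocol permits the knowledge but does not require it.
- **Repeat examinations appear to be all analysed.** A reader might infer that the operator may choose which examination counts. The autocorrelation correction in section I.2 makes sense only if recorded repeats enter the analysis together. This stands for recorded examinations. It does not reach views retaken and never recorded, or windows declared inadequate. The protocol describes no acceptance step, so these behaviours are inferred from how a scan is done.
- **Taking part in all tasks is not doing all tasks for one patient.** Section K.3 does not say that one person screens, scans and abstracts the same patient, and the case report form, which is not shown, may fix the order of entry. This stands as a caveat, but nothing in the protocol prevents the overlap in a team of three.
- **It may be late, and masking may be impracticable for some inpatients.** The version is dated 11.29.21, section F.1 expects completion in December 2021, and section M speaks of the study in the past tense. Section F.2 says that the inpatient scan guides care. Both stand and shape the fix.

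**Conclusion.** The point holds for patients whose TTE or catheterization was done before the KOSMOS scan. For them the protocol lets the operator know the value that the automated reading will be compared with, and sets no order of recording that would protect the reading. Who scans, what they may have seen and when a value is locked are rules of conduct that belong in a protocol, so an unseen analysis plan does not settle the matter.

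The direction is toward better apparent agreement. The size cannot be derived from the documents. On the assumptions above, selection in a quarter of patients narrows the limits by about 5% to 8%. A reader might take the 33% or 40% entries of the table as the likely effect; they need selection in every patient and error correlations of 0.5 or 0, and nothing in the documents supports either. Nor do the documents show that any operator used a known value; they show only that it is possible.

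**What to change.** **For reference-first patients still to be scanned:**

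- An investigator who has not opened the reference report performs the scan; another member of the existing team checks the chart and abstracts the reference.
- Every automated LVEF, stroke volume and cardiac output attempt, including failed windows, is entered in REDCap, time-stamped and locked before the reference value is opened or entered.
- The first complete reading is primary. The repeated-measurement correction in section I.2 is kept for an analysis of all recorded readings, so the existing plan is retained.
- Where masking is not possible because the scan guides an inpatient's care, the patient is flagged.

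**For all patients, including those already scanned:** report agreement separately by test order (reference before or after the scan) and state that operators were not masked. The two groups may differ in patient mix and in the interval between tests, so a difference between them is a signal and not proof of bias. The variables listed for sharing in section M include no indicator of test order. Adding one would let the pooled analysis make the same split.

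**Cost:** a protocol amendment and a change to the case report form, with no added staff. Two of the three investigators are needed for each reference-first patient, which may delay some scans.

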## K.4 IRB Review

1. *Check to confirm that an appropriate IRB registered with the OHRP, will review and approve this study.*
2. *Check to confirm that any amendments to the protocol or informed consent documents will be reviewed and approved by the IRB prior to use, unless required to eliminate an apparent immediate hazard to subjects.*

## K.5 Multi-Site Research

Is this a multi-site study where Tufts is the sponsor, primary grant recipient, or coordinating site?:

